### Intervention group

The intervention is based on the Norwegian manualized program of SW-PBIS, N-PALS (Positiv Atferd, Støttende Læringsmiljø, og Sammhandling). The Norwegian model shares its core components with the original SW-PBIS model [16]. The program’s core components constitute: (a) positive behavior support strategies, including positive expectations and classroom rules, which are followed up with positive feedback and encouragement; (b) a system for monitoring student behavior, (c) school-wide corrections using consequences, (c) instruction in classroom management skills for teachers, and (e) strategies for collaboration with parents. These components are implemented through activities at school level and at classroom level. The implementation at school level starts with establishing a leadership team, comprised of school leaders, team leaders and members of school welfare team. The leadership team assesses the needs and resources at the school and agrees on behavioral expectations and rules. The team monitors the student behaviors and provides opportunities for teacher professional development with focus on classroom management and relationship building. At classroom level, the teachers incorporate school-wide expected behaviors into their classroom instruction through classroom activities and classroom rules. The teachers also integrate their training in classroom management and relationship building in their teaching practices.

The training in the project is primarily provided through instructors, that are appointed at each school. The trainers attend online training sessions for ten afternoons over eight months. Depending on the size of the school, the schools in the SW-PBIS group send between two and ten staff members for SW-PBIS instructor training (ten training sessions, totalling 25 h). The instructors then educate and supervise the school staff, with the support of the SW-PBIS team. The instructor is in turn responsible for training and mentoring school staff in SW-PBIS. Instructors are supported in the implementation of a SW-PBIS team in the school. The team includes the school’s principal, student health staff and representatives of the school’s teams and professions. The team has two important tasks: to participate in the planning of the implementation and facilitate the work of the instructors, and to contribute to the adaptation of the program to local conditions. Instructors teach and mentor school staff 1–2 times a month (approximately 1.5 h per session) and meet regularly with the SW-PBIS team. The manual for the universal Tier 1 of the Norwegian N-PALS program was translated into Swedish and adapted to Swedish conditions [27]. The program was first pilot-tested in nine schools [28]. Prior to the implementation of the program, three instructors and two researchers ([name] and [name]) received training at the Norwegian Center for Child Behavioral Development.

### Control group

The control group in the first wave of data collection is selected in accordance with quasi-experimental design with a nonequivalent control group [29]. The teachers in the control group will, instead of a wait-list intervention, receive a shortened version of SW-PBIS, containing only classroom management. The schools that are part of the classroom management group also send staff for instructor training (ten training sessions, 25 h in total, just as much as the SW-PBIS schools). Similar to the SW-PBIS group, the instructors in this group educate and supervise school staff, supported by a team at the school. Both groups have access to a manual and supporting materials. This design does not pose threats to the internal validity of the study, as classroom management is one of principles of PBIS framework. In this way it will be possible to explore the specific contribution of SW-PBIS in contrast to classroom managment only. Control group in the second wave of data collection constitutes a wait-list control group and will not be engaged in any kind of intervention during the intervention period.

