## Aim

The aim of the project is twofold. Firstly, the aim is to evaluate the effectiveness of SWPBIS program for students’ social-emotional skills and academic achievement as well teachers’ and students’ perceptions of learning environment and to explore how school-level factors may moderate or mediate the effect of SWPBIS on the outcomes. Secondly, the aim is to get a deeper understanding of the social processes and local meanings that emerge and take form among the students, teachers and other school professionals as they participate in the SW-PBIS program. The aims are specified in four research questions.

What are the effects of SW-PBIS program on students’ social-emotional skills and academic achievement as well teachers’ and students’ perceptions of learning environment?To what extent do school level factors mediate and moderate the effects of the SW-PBIS program on the study outcomes over time?How are the central contents of the SW-PBIS program made sense of and negotiated in school teams and classrooms at two schools during the course of program implementation?How do specific instances of student-teacher interaction lead to changes in students’ behavior and responses to the SW-PBIS program, and what forms of ethical dilemmas evolve in the management of behavior problems in classrooms?

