### Participants

The study will be conducted in compulsory schools and include classes from grade one to grade nine. Inclusion criteria for the intervention and control groups are: (a) compulsory school, grades 1–9; (b) the school have not been previously enrolled in an SW-PBIS program by other providers (b) principal, teachers, students and their parents consent to participate in the study. Each of the two waves of recruitment in the study will include 80 schools. According to estimations with the software Optimal Design [25], 62 schools are required, based on an effect size of 0.25 and a power of 80%, with an expected amount of 12 classes per school, 20 students per class and an intraclass correlation (ICC) of 0.10 at school level and 0.05 at classroom level [26]. To account for 20% attrition, 80 schools are needed. Based on previous studies of SW-PBIS in the European context [14, 32], we expect Cohen’s d effect size of 0.20 to measure an important difference between the intervention and control group.

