### Recruitment

Information about the study will be distributed by e-mail to all compulsory schools in Sweden. The e-mail lists will be retrieved from Swedish National Agency for Education. In addition, information about the study will be distributed at conferences and via regional principal and teacher networks. School principals and teachers will be invited to online meetings at which detailed information about the study will be presented and detailed information on participation in the study will be provided. Upon enrollment in the project, the information and invitation to participate in the study is distributed to students’ guardians. In addition to Swedish language, information about the study will be presented in ten frequent languages in Sweden (Arabic, Spanish, English, Somali, Serbo-Kroatian, Polish, Kurdish, Finnish, Farsi, and Urdu). Students in grade 9 will also be asked for informed consent, upon consent from both guardians.

In the first wave of recruitment, the decision to allocate participants to intervention or control group will be based on the school principals’ choice of intervention. The schools, catering for students in grades 4–9, which have expressed interest in the intervention, will be stratified in three groups, based on size, parent educational level, proportion of students with migrant background and students’ average achievement rates. This information is publicly available from SALSA database of the National Agency for Education. After stratification, schools within each stratum will be assigned to intervention group. The same procedure will be conducted in the recruitment of control groups. In the second wave of recruitment, the participants from schools grades 1–9 will be recruited the study, and then randomly allocated to either intervention or control group.

According to estimations with the software Optimal Design (OD; Spybrook et al., 2011), 62 schools are required, based on an effect size of 0.25 and a power of 80% with an expected amount of 12 classes per school, 20 students per class and an intraclass correlation (ICC) of 0.10 at school level and 0.05 at classroom level (Hedges & Hedberg, 2007). To account for 20% attrition, 74 schools are needed (approximately 17 280 students). Therefore, in each wave of data collection, a minimum of 74 schools will be recruited.

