## Discussion

The study aims to evaluate the effectiveness of SW-PBIS program for students’ social-emotional skills and academic achievement as well teachers’ and students’ perceptions of learning environment. Furthermore, the study intends to explore how school-level factors may moderate or mediate the effect of SW-PBIS on the outcomes. We hypothesize that the effects of SW-PBIS may vary dependent on school-level factors characterizing the schools participating in the project. The strength of the study further lies in the combination of quantitative and qualitative methods, which may enable us to understand possibilities and challenges for implementation of SW-PBIS program in varied school contexts and relate it to study outcomes. The challenge of the study lies in the fact that the implementation of SW-PBIS is extended over a longer period of time at the same time as it is difficult to retain control groups over such extended periods of time. Therefore, two waves of recruitment are used, in which active control group is retained over two years while wait-list control group is retained over a school year. The advantage in the first wave of recruitment is that it allows for a longer term evaluation, but the challenge is the lack of full experimental control. The advantage in the second wave of recruitment is that it allows for experimental control but is restricted to a short term evaluaton of the SW-PBIS model.

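### Wave 1 estimates what SW-PBIS adds to classroom management training, one of its own components, but it is sized and described as if it measured the programme's full longer-term effect

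*Protocol article*

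**What the plan says.** The Control group section states that teachers in wave 1 control schools "receive a shortened version of SW-PBIS, containing only classroom management". These schools also send staff to ten instructor sessions (25 hours, the same as the SW-PBIS schools), have a supporting team in the school and receive a manual. The same section says that the design allows the specific contribution of SW-PBIS over classroom management alone to be explored. Wave 2 controls are a wait-list group with no intervention during the study period.

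The Intervention group section lists "instruction in classroom management skills for teachers" among the core components of SW-PBIS.

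The first research question in the Aim section begins "What are the effects of SW-PBIS program on students" and names neither a comparator nor a wave. It covers social-emotional skills, academic achievement and the learning environment.

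The Participants section says "62 schools are required, based on an effect size of 0.25", and the Recruitment section repeats that calculation and applies it to both waves: "Therefore, in each wave of data collection, a minimum of 74 schools will be recruited". The Participants section also expects an "effect size of 0.20 to measure an important difference between the intervention and control group", again without naming a wave or comparator.

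The Discussion says "The advantage in the first wave of recruitment is that it allows for a longer term evaluation" and names the lack of full experimental control as the challenge. In Table 1, national-test results are collected in wave 1 only.

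**The concern.** The two waves estimate different quantities. Wave 2 sets SW-PBIS against no programme. Wave 1 sets it against one of its own components, delivered with the same hours of instructor training. If classroom management training works, the wave 1 difference is smaller than the total effect of SW-PBIS, and a programme that works could show little difference in wave 1.

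The Control group section recognises this contrast, but the research question, the sample-size statement and the Discussion do not carry it through. Two consequences follow:

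- **Interpretation.** A small or null wave 1 difference could be taken as absence of a lasting effect. A wave 1 estimate below the wave 2 estimate could be taken as fading over time, although the comparator changed as well as the duration.
- **Power.** The 0.25 used for sizing has no stated basis as an increment over an active comparator.

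**Working it through.** **1. Which outcome has which comparator**

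| Question | Wave 1 | Wave 2 |
|---|---|---|
| Comparator | Classroom management training | Wait-list, no intervention |
| Allocation | Principals' choice | Random |
| Duration | Two years, three time points | One school year, two time points |
| National tests | Yes | No |

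The two-year effect and national-test achievement appear only in the wave 1 column, so neither has an untreated control group. The Students' achievement paragraph adds a comparison with the national average, which is an external benchmark and not a study control group.

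**2. Inputs for power**

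From Participants and Recruitment: effect 0.25, power 80%, 12 classes per school, 20 students per class, ICC 0.10 for school and 0.05 for classroom, 62 schools before attrition. The Participants section plans 80 schools per wave. Assumed, because not stated: two-sided 5%, 1:1 allocation, no covariate adjustment.

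**3. The plan's own figure**

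Variance per school mean, in SD units:

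v = 0.10 + 0.05/12 + 0.85/240 = 0.1077

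Standard error of the difference with K schools: SE = √(4v/K).

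Normal approximation: K = 4 × 0.1077 × (1.960 + 0.842)² / 0.25² = 54.1, which becomes 56 as an even number of schools. The noncentral t with K − 2 degrees of freedom gives 58. The stated 62 is not reproduced exactly, but it errs on the safe side. With K = 62, SE = √(0.4308/62) = 0.0834, the noncentrality at 0.25 is 0.25/0.0834 = 3.00, and power is 84%.

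**4. Power for smaller increments**

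Suppose classroom management alone delivers a share f of a total effect of 0.25. The contrast is then 0.25 × (1 − f). The article gives no f, so these are scenarios. With K = 80, SE = √(0.4308/80) = 0.0734.

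| f | Contrast | Power, 62 schools | Power, 80 schools |
|---|---|---|---|
| 0 | 0.25 | 84% | 92% |
| 20% | 0.20 | 66% | 77% |
| 25% | 0.1875 | 60% | 71% |
| 50% | 0.125 | 31% | 39% |

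The smallest contrast with 80% power is about 0.24 with 62 schools and about 0.21 with 80.

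**5. Sensitivity to the unreproduced 62**

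If v is set so that 62 schools give exactly 80% at 0.25 (v = 0.1195), power with 62 / 80 schools is 61% / 72% at 0.20 and 29% / 36% at 0.125. The pattern is unchanged.

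**The case against.** The comparator is not hidden. The Abstract, the Methods, the Control group section and the Discussion all say that wave 1 has an active control group and wave 2 a wait-list, and the Control group section states the wave 1 contrast openly. This stands: the sections do not contradict one another. What is missing is the consequence for the research question, the sizing and the conclusion.

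A reader might infer that wave 1 lacks its stated power. The article does not support that. The stated power is for 0.25, and at 0.25 it is met. Any shortfall depends on an increment below about 0.24, for which the article gives no value. A two-year total effect larger than 0.25 would offset part of what the comparator removes, and adjustment for baseline scores could raise power above the figures shown.

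A reader might also infer that the trial cannot answer its first research question. That goes too far: the question names no comparator, and wave 2 addresses the effect against no programme over one school year.

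Nor does any section plan to pool the waves or to read a difference between them as fading. That risk comes from how the Discussion pairs the waves as longer and shorter term, not from a planned analysis.

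An active control is also a defensible choice, made because control schools are hard to retain for two years. The point does not dispute that choice.

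**Conclusion.** The point holds as a matter of what wave 1 estimates and how it is described. Wave 1 can show whether SW-PBIS does better than classroom management training over two years. It cannot give the total two-year effect, or the effect on national tests, against an untreated control group. A null wave 1 result would leave open that both programmes work.

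On power, the conclusion is limited: 80% is supported for increments of about 0.24 or more with 62 schools, and no reason is given why the increment over an active comparator should be that large. The size of any shortfall rests on the assumed increment and on the test, allocation and covariate assumptions listed above.

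The gap between the 0.25 used for sizing and the 0.20 that the Participants section expects is a separate matter. It affects both waves, so the 80% figure should not be taken as secure for wave 2 either until the two values are reconciled.

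**What to change.** - **Aim.** State the first research question by wave. Wave 2: SW-PBIS versus no programme over one school year. Wave 1: SW-PBIS versus classroom management training over two years, including national tests.
- **Participants and Recruitment.** For wave 1, replace the single 80% statement with power over a range of increments below 0.25, with the test and allocation assumptions stated. Reconcile 0.25 with 0.20 before repeating the 80% figure for wave 2.
- **Discussion.** Describe wave 1 as a longer-term evaluation of the increment over classroom management. Say that a null result there is not evidence that SW-PBIS has no effect, and that a difference between the wave 1 and wave 2 estimates cannot be read as long versus short term.

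The cost is a change of wording in these sections and a less favourable power statement for wave 1. The design, the data collection and the number of schools stay as they are.

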### Outcome measures

Outcome measures encompass both individual-level and school-level measures. Individual-level measures constitute the primary outcome of the intervention, as the intention in the study is to evaluate whether the intervention benefits the participating students, while school-level variables are primarily used to explain the potential effect of the intervention. All the outcomes are assessed by researchers using a survey methodology. See Table 1 for a list of all measurement points.

**Table 1 Tab1:** Data on outcome measures at both individual and school level will be used

	2023	2024	2025
**Wave 1 Recruitment**			
Social skills improvement system – SEL Brief and Mental Health Scales – Teacher Form	x	x	x
Learning environment – Teacher and Student Questionnaire	x	x	x
Students’ achievement in national tests	x		x
Teacher Collective Self-efficacy	x	x	x
Problem behavior in classroom and school	x	x	x
**Wave 2 Recruitment**			
Social skills improvement system – SEL Brief and Mental Health Scales – Teacher Form		x	x
Learning environment – Teacher and Student Questionnaire		x	x
Teacher Collective Self-efficacy		x	x
Problem behavior in classroom and school		x	x

### Individual level measures

At individual level measures constitute teacher ratings of students’ social-emotional skills, behavior problems and academic competence, using Social Skills Improvement System – SEL Brief and Mental Health Scales, Teacher K-12 Form [33] as well as teacher and student questionnaires of classroom learning climate [32, 34].

**Social emotional skills.** Social Skills Improvement System – SEL Brief and Mental Health Scales, Teacher K-12 Form [33] contains 20 items related to five competency domains (self-awareness, self-management, social awareness, relationship skills, and responsible decision making) and 10 items encompassing emotional behavior concerns (internalizing and externalizing concerns). Examples of items are “Asks for help when needed” for social-emotional skills competency domains and “Withdraws from others” for emotional behavior concerns. The items are measured on a 4-point scale (1 = Never, 2 = Seldom, 3 = Often, 4 = Almost always). The measures have proved to have sufficient validity and reliability in previous studies [35, 36].

**Classroom learning environment.** A comprehensive assessment of the classroom learning environment is conducted using questionnaires for teachers and students [32, 34]. The teacher questionnaire consists of 14 statements, rated on a 4-point scale (1 = does not fit to 4 = fits completely), assessing various aspects of the classroom learning climate. The student questionnaire includes 22 statements, also rated on a 4-point scale, gauging students’ perceptions of the classroom environment. An example of an item in the teacher questionnaire is “There is a good working climate during lessons”. An example of an item in the student questionnaire is “Students in this class are active and interested during lessons”.

**Students’ achievement.** In addition, for the first wave of recruitment, students’ achievement on national tests of Swedish and mathematics will be retrieved from register data provided by Statistics Sweden. The data will be standardized across tests and compared with regard to the national average for those students who enter the project in grade 4 and 7 (national tests in grade 3 and grade 6) and finish the project in grade 6 and 9 (national tests in grade 6 and grade 9).

### School level measures

At school level measures encompass Teacher Collective Self-efficacy [30], and school level measures of problem behavior [31, 32].

**Collective self-efficacy.** The Collective Self-efficacy questionnaire (CES; 30) will be used as a measure of teacher collective beliefs of possibilities to influence student learning. CES contains 21 items and a 6-point scale is used (from 1 = Do not agree at all, 2 = Do not agree, 3 = Do not agree fully, 4 = Agree a little, 5 = Agree, 6 = Agree completely). An example of item is “Teachers in this school are able to get through to difficult students”. In previous studies, collective self-efficacy has shown to be influenced by SW-PBIS programs [16].

**Problem behavior in classroom and school.** The Problem Behavior in the Classroom Last Week scale (20 items) is used to collect reports of disruptive behavior in the classrooms on a 5-point Likert scale from 0 (not observed) to 5 (observed several times per day) [31, 32]. The Problem Behavior in the School Environment scale [31, 32] is a school level measure containing 15 items and similar rating alternatives. Examples of behaviors in the scales are “Destroying school environment” or “Physical aggression towards peers and teachers”. The scales have shown satisfactory psychometric properties in prior studies in Norway [e.g., 32].

### Implementation fidelity

To measure implementation fidelity of the SW-PBIS Tier 1, the members of school leadership team will be asked to complete questionnaire Benchmarks of Quality [37] each year. The questionnaire is a self-evaluation tool that supports school professionals in monitoring progress of implementation of SW-PBIS Tier 1. BoQ contains 53 items, divided into 10 subscales covering team functioning, staff commitment, expectations and discipline procedures. Each item can be rated on a 3-point scale (1 = Not yet, 2 = Can be better, 3 = Is in place). The items are summarized in a total score.

